## Abstract

**Background:**

Colorectal surgery is frequently complicated by surgical site infections (SSIs). The most important consequences of SSIs are prolonged hospitalization, an increased risk of surgical reintervention and an increase in mortality. Perioperative intravenously administered antibiotic prophylaxis is the standard of care to reduce the risk of SSIs. In the last few decades, preoperative orally administered antibiotics have been suggested as additional prophylaxis to further reduce the risk of infection, but are currently not part of routine practice in most hospitals. The objective of this study is to evaluate the efficacy of a preoperative orally administered antibiotic prophylaxis (Pre-OP) in addition to intravenously administered perioperative antibiotic prophylaxis to reduce the incidence of deep SSIs and/or mortality after elective colorectal surgery.

**Methods/design:**

The PreCaution trial is designed as a multicenter, double-blind, randomized, placebo-controlled clinical trial that will be carried out in The Netherlands. Adult patients who are scheduled for elective colorectal surgery are eligible to participate. In total, 966 patients will be randomized to receive the study medication. This will either be Pre-OP, a solution that consists of tobramycin and colistin sulphate, or a placebo solution. The study medication will be administered four times daily during the 3 days prior to surgery. Perioperative intravenously administered antibiotic prophylaxis will be administered to all patients in accordance with national infection control guidelines. The primary endpoint of the study is the cumulative incidence of deep SSIs and/or mortality within 30 days after surgery. Secondary endpoints include both infectious and non-infectious complications of colorectal surgery, and will be evaluated 30 days and/or 6 months after surgery.

**Discussion:**

To date, conclusive evidence on the added value of preoperative orally administered antibiotic prophylaxis in colorectal surgery is lacking. The PreCaution trial should determine the effects of orally administered antibiotics in preventing infectious complications in elective colorectal surgery.

**Trial registration:**

Netherlands Trial Register, ID: NTR6113. Registered on 11 October 2016; EudraCT 2015-005736-17.

**Electronic supplementary material:**

The online version of this article (doi:10.1186/s13063-018-2439-4) contains supplementary material, which is available to authorized users.

## Background

Surgical site infections (SSIs) are the most common hospital-acquired infections in surgical patients [1, 2]. SSIs are associated with extended hospitalization and are an important source of readmissions and surgical reintervention [2–4]. Relative to other surgical procedures, the incidence of SSIs is highest after colorectal resections, affecting up to 15% of all patients [5]. Despite extensive efforts that have been made in improving infection control practice, the incidence of SSIs after colorectal surgery remains unaffectedly high, whereas the incidence appears to have declined in other surgical specialties [6]. This persisting infection rate highlights the need to explore novel measures to reduce SSIs after colorectal procedures.

To establish new infection prevention measures, it is important to understand the pathogenesis of SSIs. The development of these infections is preceded by microbial contamination of the surgical site [7]. The colon and rectum are densely colonized by microorganisms which explains the high postoperative infection rate [8, 9], as well as the finding that the microorganisms that are most frequently isolated from colorectal SSIs are also the colonizing species [10–12].

An important measure to reduce the risk of postoperative infections is to intravenously administer perioperative prophylactic antibiotics that cover these species, conforming to the national infection control guidelines [13]. For colorectal surgery, orally administered antibiotics can be applied in addition to the intravenously administered prophylaxis. This prophylaxis contains non-absorbable antibiotics, such as neomycin combined with erythromycin or metronidazole, that are administered 1 to 2 days prior to the surgical procedure. The non-absorbable nature of these antibiotics implies almost complete absence of systemic uptake after oral intake. The antibiotics, therefore, only exert local activity in the gastrointestinal tract with low risks of side effects. The rationale of combining systemic and oral prophylaxis is that orally administered antibiotics reduce the colonic bacterial contamination levels directly at the surgical site, whereas systemic antibiotics are used as a safeguard by establishing effective antibiotic concentrations in the soft tissues to minimize the risk of infection and to prevent perioperative endotoxinemia. Despite the beneficial effects of the addition of orally to intravenously administered prophylaxis in preventing infections in individual studies, the oral administration of antibiotics is currently not recommended in international infection control guidelines because of large variability in the antibiotic regimens tested and the limited availability of high-quality studies [14].

The oral administration of antibiotics to reduce the colonic bacterial load became popular as surgical prophylaxis for colorectal surgery in the 1970s [8]. At that time it was believed that orally administered antibiotics would only be effective when the colon was simultaneously cleansed of its contents. Therefore, mechanical bowel preparation (MBP), a technique that involves the administration of osmotic substances to induce voiding of the intestinal contents, was introduced and combined with the preoperative oral administration of antibiotics [9, 15] This combination became standard of care in colorectal surgery. Since then, several studies have questioned the necessity and safety of MBP [15, 16]. Recent meta-analyses have concluded that the use of MBP prior to colorectal surgery could be safely omitted, as MBP alone had no overall beneficial effect on postoperative complications and caused substantial discomfort for the patient [17–21]. Furthermore, MBP has been associated with an increase in inflammatory processes, or with spillage of liquid bowel contents when bowel preparation was performed inadequately resulting in an increase in postoperative infections [16, 22]. Therefore, MBP is no longer recommended in the international guidelines for colorectal surgery. The practice of MBP was also abandoned as the pre-surgical admission period has continuously decreased, precluding these preoperative preparations. The oral administration of antibiotics in an uncleansed colon was thought to be ineffective, resulting in the simultaneous disappearance of oral bowel cleansing and orally administered antibiotic prophylaxis [23].

A recent Dutch single-center, randomized, placebo-controlled trial (RCT) provided new insights into the use of orally administered antibiotics as a surgical prophylaxis prior to gastrointestinal surgery [24]. Instead of using the common regimens for orally administered prophylaxis consisting of tablets, the efficacy of a combination of non-absorbable antibiotics in a suspension was investigated. This suspension contained tobramycin, colistin and amphotericin B and is also used in selective decontamination of the digestive tract (SDD), an infection control measure implemented on intensive care units (ICUs). This study reported a 36% reduction of the incidence of infectious complications and anastomotic leakage in patients receiving the preoperative antibiotic prophylaxis. However, the study included patients who underwent all types of gastrointestinal procedures (*N* = 294). Colorectal procedures were analyzed as a subgroup, resulting in limited statistical power. Furthermore, MBP was frequently administered to patients undergoing colorectal procedures. Nevertheless, the results of this study are promising and encourage further research to confirm the benefit of using orally administered prophylaxis.

In conclusion, the high incidence of SSIs after colorectal surgery and its associated morbidity and mortality justifies the evaluation of new preventive approaches. Preoperative orally administered antibiotic prophylaxis, in addition to standard perioperative intravenously administered prophylaxis, may reduce the incidence of SSIs after colorectal surgery. However, data on its efficacy without the concurrent practice of MBP are lacking [25]. A randomized, double-blind, placebo-controlled clinical trial is, therefore, warranted.

## Methods/design

### Study hypothesis and objectives

The objective of this trial is to determine the efficacy of preoperative orally administered antibiotic prophylaxis (Pre-OP) in addition to perioperative intravenously administered antibiotic prophylaxis on the incidence of deep SSIs and/or mortality after elective colorectal surgery. We hypothesize that Pre-OP will result in a relative reduction of the risk of deep SSIs and/or mortality of at least 40%.

### Study design and setting

The PreCaution study is designed as a double-blind, randomized, placebo-controlled, multicenter trial. The study will be conducted in Dutch university and non-university hospitals. Study centers will be eligible to participate in the study if antibiotic prophylaxis other than the perioperative intravenously administered prophylaxis is not part of the standard perioperative care for colorectal surgery. Patient enrollment started in April of 2017 and is expected to be completed within 18 months after the start of the study.

### Study population

#### Eligibility criteria

Participants will be drawn from a population of adult patients who will undergo elective colorectal surgery. Patients with an absolute contraindication for the study medication, such as pregnant women or nursing mothers, patients with a previously diagnosed allergy for the antibiotics in the study medication or patients with myasthenia gravis, are excluded from participation. Inclusion and exclusion criteria are presented in Table 1.

**Table 1 Tab1:** Inclusion and exclusion criteria

Inclusion criteria	Exclusion criteria
Adult patients undergoing elective colorectal surgery	Age < 18 years Legally incapacitated patients Patients who are unable to sign informed consent Patients who have an inability to take medication orally Patients who have undergone abdominal surgery within 30 days before randomization Patients with a documented allergy to colistin or aminoglycoside antibiotics Pregnant women or nursing mothers Patients diagnosed with myasthenia gravis Patients with a pre-existent stoma Patients who previously participated in the PreCaution trial or patients who already received study medication but for whom surgery was postponed for more than 7 days

#### Sample size

The sample size is calculated to be 966 patients, based on a one-sided type I error of 2.5%, a type II error of 20% and an assumed 40% reduction on the absolute risk for the primary outcome in the intervention group. The absolute risk of the primary outcome is assumed to be 14%. Furthermore, one interim analysis will be conducted halfway using O’Brien-Fleming type of boundaries, with the possibility of stopping the trial for efficacy in case of overwhelming treatment effect. The absolute risk and the 40% relative risk reduction based on unpublished data from a 4-year survey of a Dutch teaching hospital, where identical preoperative orally administered antibiotic prophylaxis was introduced as standard of care.

#### Evaluable patients

Patients who start with the 3-day intervention period but for whom surgery is cancelled or postponed for more than 7 days, will not be evaluable for analysis of the primary and secondary outcomes. Sample size calculations are based on evaluable patients and, herewith, assumes replacement of all non-evaluable patients. A limit of 7 days is chosen as a cut-off to ensure that patients are not re-colonized at the time of surgery, since it is expected that the effects of decontamination will last for a least several days when the 3-day treatment course is completed.

### Assignment of interventions

#### Randomization

After enrollment, patients will be randomly assigned to one of two treatment arms in a 1:1 ratio.

The randomization will be performed using a permuted block design with varying block sizes and stratification per study center. An independent pharmacist form Stichting Apotheek Haarlemse Ziekenhuizen, who will also be in charge of the production of the study medication, will perform the randomization. The pharmacy will provide the study medication in identical containers that will be sequentially numbered with unique medication numbers. These numbers will correspond to the treatment allocation, and will be documented on the allocation list. This list will be guarded by the hospital pharmacist of the Amphia Hospital (Breda, The Netherlands) who will coordinate the distribution of the study medication to the study centers. Members of the local study teams will be instructed to distribute the study medication according to the allocation sequence. The unique study medication identification numbers will be linked to the subjects at enrollment on a subject identification log.

#### Blinding

Patients, treating physicians and individuals assessing the study outcomes will be blinded to the treatment assignments for the duration of the study. Treatment assignments will be revealed when all patients have completed their 6-month follow-up period.

Individual unblinding will be considered only when the treating physician deems knowledge of the treatment assignment essential for the safety of the patient. Any intentional or unintentional breaking of the blinding will be reported to the sponsor.

### Treatment of subjects

#### Intervention

All patients will receive the study medication as part of the intervention. The intervention can either be treatment with active medication (Pre-OP) or a placebo. Pre-OP is a transparent solution that consists of two antibiotic components: colistin sulphate (20 mg/mL) and tobramycin (16 mg/mL). Placebos are manufactured without the active antibiotic components. The placebo solutions contain flavoring additives and colorants to mimic the taste and color of Pre-OP. All patients will receive perioperative intravenously administered prophylaxis according to the national infection prevention guidelines [26].

#### Dosage and route of administration

Patients are instructed to take the study medication four times daily, during the last 3 days prior to surgery. Each dose consists of 5 mL of either Pre-OP or placebo. In the case of Pre-OP, this represents 100 mg of colistin sulphate and 80 mg of tobramycin.

### Outcome measures

As a primary composite endpoint, we will investigate the efficacy of Pre-OP on deep SSI and/or mortality within 30 days after surgery. The secondary endpoints including their definitions are summarized in Table 2.

**Table 2 Tab2:** Definition of endpoints

Endpoints	Definitions
Primary composite endpoint	
Cumulative incidence of deep surgical site infection and/or mortality within 30 days after surgery	Deep SSI will be diagnosed according to the CDC criteria for surgical site infections [37]. Deep SSI includes both deep incisional SSI and organ/space SSI
Secondary endpoints	
*30 days after surgery*	
Cumulative incidence of superficial SSI	Superficial and deep SSIs will diagnosed according to the CDC criteria for surgical site infections [37]
Cumulative incidence of deep SSI	
All-cause mortality	
Cumulative incidence of bacteremia	Blood cultures positive for microorganisms
Cumulative incidence of infection with *Clostridium difficile*	Stool sample positive for *C. difficile* toxins
Cumulative incidence of infection with HRE	Clinical cultures positive for ESBL or carbapenemase-producing *Enterobacteriaceae* or *Enterobacteriaceae* resistant to quinolones and/or aminoglycosides [38]
Cumulative incidence of rectal colonization with HRE and colistin resistant species	Rectal swabs positive for HRE or colistin resistant species, measured at baseline and 30 days after surgery
Cumulative incidence of anastomotic leakage	Clinical and/or radiological evidence of leakage requiring surgical or radiological reintervention
Cumulative incidence of re-laparotomy	Reoperation in the abdominal region
In-hospital use of antibiotics	Defined as “days on therapy”
*6 months after surgery*	
All-cause mortality	
Quality of life	Measured with the RAND-36 questionnaire [39]
Length of hospital stay	In days, including all readmissions
Length of ICU stay	In days, including all readmissions
In-hospital costs	

*CDC* Centers for Disease Control and Prevention, *ESBL* extended-spectrum beta-lactamase, *HRE* highly resistant *Enterobacteriaceae*, *ICU* intensive care unit, *SSI* surgical site infection

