^a^The day of surgery is referred to as day 0. The exact time points of the first and second preoperative visits to the outpatient clinic will depend on the local schedules and procedures

^b^Screening and enrollment are performed during visits to the outpatient clinic. These visits are not study-specific and are planned according to the local logistics

^c^The postoperative data collection is performed by assessment of the patient registers. A phone call will be made at around day 30 and month 6 to assess the status of the patient and to remind the patient to perform the rectal swab (day 30) and fill in the questionnaire (month 6)

Patients will be followed until 6 months after surgery to evaluate the development of primary and secondary outcomes. The data on almost all of these outcomes, including infectious complications will be documented as part of daily practice. Thirty days after surgery, the medical records will be assessed to collect data on primary and secondary outcomes and a second rectal swab will be taken by either the patient or by a member of the local study team. Six months after surgery, the medical records will be assessed again to collect additional data on readmissions and length of hospital stay, including admissions to the ICU. Furthermore, patients will receive the second quality-of-life questionnaire. After the questionnaire has been completed and sent back to the study team, the follow-up is completed.

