#### Microbiological methods

Clinical cultures will be performed and processed in the local microbiology laboratory of the participating centers according to the routine laboratory procedures. Date of culture, specimen type, species cultured, antimicrobial susceptibility and the production of extended-spectrum beta-lactamase or carbapenemase will be documented. Fecal samples from patients who develop nosocomial diarrhea will be tested for the presence of *Clostridium difficile* toxins, according to routine laboratory procedures and based on the indication by the attending physician.

Rectal swabs will be pre-enriched and subsequently cultured using selective media, aimed at the detection of extended-spectrum beta-lactamase (ESBL)-producing *Enterobacteriaceae* and carbapenem-, tobramycin- and colistin-resistant, Gram-negative bacterial species’ identification and antimicrobial susceptibility testing will be performed for all isolates that grow on either one of the screening agars. Phenotypic ESBL confirmation will be performed with the combination disk diffusion method according to the NVMM guideline on the laboratory detection of highly resistant microorganisms (HRMO).

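### Bacteremia is defined as any positive blood culture, so likely skin contaminants count as events; incidence is inflated, and the risk ratio is diluted if both arms are cultured about equally often

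*Protocol article*

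**What the plan says.** In the protocol article, Table 2 (Outcome measures) lists "Cumulative incidence of bacteremia" among the secondary endpoints at 30 days. Its whole definition is "Blood cultures positive for microorganisms". No organism list, minimum number of positive cultures, clinical criterion or contaminant rule appears there or elsewhere in the article.

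Other rows of the table are more specific. For surgical site infection, "Deep SSI will be diagnosed according to the CDC criteria for surgical site infections". Anastomotic leakage must have led to a reintervention, and infection with resistant Enterobacteriaceae is tied to named resistance types.

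On how the data arise, Microbiological methods states: "Clinical cultures will be performed and processed in the local microbiology laboratory of the participating centers according to the routine laboratory procedures". The items documented for each culture include "Date of culture, specimen type, species cultured, antimicrobial susceptibility". Study procedures adds: "The data on almost all of these outcomes, including infectious complications will be documented as part of daily practice". Under Blinding, "Patients, treating physicians and individuals assessing the study outcomes will be blinded to the treatment assignments".

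**The concern.** A positive blood culture may reflect bacteria in the bloodstream or skin organisms introduced when the sample was drawn. The trial tests whether lowering the bacterial load of the colon and rectum prevents infection, and contamination at sampling lies outside that mechanism. The definition counts both kinds of result alike. Taken literally, its reference to microorganisms also makes a fungal culture a bacteremia.

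Two things are at stake. The reported incidence will be too high in any arm with contaminated cultures. The comparison between arms will also mix the effect on true bacteremia with a component that depends on how many cultures are taken. For an uncommon binary outcome, false positives spread evenly over the arms move the risk ratio towards 1 and cost power, even though they are non-differential.

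**Working it through.** **Figures in the plan.** The article gives no rate, effect or power for bacteremia, so there is no figure of its own to reproduce. From Sample size I take only the total of 966 (483 per arm at 1:1) and the one-sided 2.5% level. As a check of the power formula (two proportions, pooled variance under the null), the plan's primary-endpoint inputs of 14% against 0.6 × 14% = 8.4% with 483 per arm give 78.9%, close to the stated 80%.

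**Assumptions, none from the documents.** True placebo risk p = 4-6%; true risk ratio (RR) 0.60; risk c = 1-3% that a patient without true bacteremia has a contaminated culture. True bacteremias are taken as all detected.

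**Step 1: equal contamination in both arms.** Observed risk = p + c(1 − p). For p = 4% and c = 2%:
- Placebo: 0.04 + 0.02 × 0.96 = 0.0592.
- Pre-OP: 0.024 + 0.02 × 0.976 = 0.0435.
- RR = 0.0435 / 0.0592 = 0.74 instead of 0.60.
- Contaminants make up 0.0192 / 0.0592 = 32% of placebo events and 0.0195 / 0.0435 = 45% of Pre-OP events.

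Expected RR, with power in brackets:

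| True placebo risk | c = 0 | c = 1% | c = 2% | c = 3% |
|---|---|---|---|---|
| 4% | 0.60 (29%) | 0.68 (23%) | 0.74 (20%) | 0.77 (17%) |
| 5% | 0.60 (35%) | 0.67 (29%) | 0.72 (25%) | 0.75 (22%) |
| 6% | 0.60 (41%) | 0.66 (35%) | 0.70 (31%) | 0.74 (27%) |

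**Step 2: risk difference under equal contamination.** Observed difference = true difference × (1 − c). At p = 4% and c = 2% it goes from 1.60 to 1.57 percentage points. The loss is 1-3% of its value over the range of c.

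**Step 3: contamination that follows culturing.** Cultures are clinical and not scheduled, so let c = q × r in each arm. Here q is the share of patients cultured and r the share of those with a contaminated result. Assume p = 4%, 30% of placebo patients cultured, and r = 2% or 5%, which gives c = 0.6% or 1.5% on placebo. The true values are RR 0.60 and a difference of 1.60 points.

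| Cultured on Pre-OP | RR, r = 2% | RR, r = 5% | Difference in points, r = 2% / 5% |
|---|---|---|---|
| 30% (equal) | 0.65 | 0.71 | 1.59 / 1.58 |
| 20% | 0.61 | 0.62 | 1.79 / 2.06 |
| 18% (40% fewer) | 0.60 | 0.60 | 1.82 / 2.16 |
| 10% | 0.57 | 0.53 | 1.98 / 2.55 |

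Dilution of the RR is greatest with equal culturing, disappears when culturing falls by the same 40% as bacteremia, and reverses beyond that. The near-immunity of the risk difference in Step 2 holds only under equal contamination. Once culturing differs between arms, the difference is overstated.

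**The case against.** **Direction.** It is tempting to infer that contaminants add the same number of false events to each arm, so that the estimate must move towards no difference. The documents do not support this. Blinding makes the contamination risk per culture independent of arm, but not the number of cultures. Cultures follow routine care, and a prophylaxis that works could mean fewer of them. This part of the objection stands in full, and the pull towards 1 is conditional.

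**Size and scale.** Every bacteremia, contamination and culturing rate here is assumed. The culturing model gives c of 0.6-1.5%, so the upper end of the 1-3% range may be pessimistic. The article does not name the risk ratio as the effect measure for secondary outcomes. It does list logistic regression, however, and at these risks the odds ratio behaves much like the RR. At p = 4% and c = 2% it goes from (0.024/0.976)/(0.04/0.96) = 0.59 to (0.0435/0.9565)/(0.0592/0.9408) = 0.72.

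**Consequence.** Power is at most about 41% in these scenarios even with no contaminants. A null result on bacteremia would be weak evidence under either definition and could not be blamed on contamination alone.

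**Available data.** One might infer that the protocol already records everything a stricter definition needs. It lists species and date, but not the number of separate draws, and the eCRF is in an additional file not shown here. This stands, and the fix must allow for it.

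**Condensed article.** Table 2 is presented as a summary, and a rule for commensals could sit in a fuller document. But the table does state a definition, and followed as written it counts contaminants. A positive culture is also a simple, reproducible criterion across centers, which is a reason to keep it as a sensitivity result.

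**Conclusion.** The concern holds in a limited, conditional form. As stated, the definition counts likely skin contaminants as bacteremia, and the reported incidence is inflated wherever such cultures occur. With about equal culturing in both arms, and under the assumed rates (true placebo risk 4-6%, true RR 0.60, contaminants in 1-3% of patients per arm), the expected RR is 0.66-0.77 and power falls, for example from 35% to 29% at a 5% true risk and 1% contaminants. The risk difference then loses only 1-3% of its value. If Pre-OP reduces culturing, the dilution of the RR is smaller, absent or reversed.

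An unconditional bias towards no difference is therefore not shown. What is shown is that the endpoint partly measures how often blood is drawn. The matter is minor: one secondary endpoint with low power under either definition, and no effect on the primary endpoint or the sample size of 966.

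**What to change.** Before treatment assignments are revealed, define bacteremia as either:
- a recognised pathogen in at least one blood culture; or
- the same common skin commensal in two or more separate cultures. If separate draws on one day are not recorded, require different culture dates.

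List in advance which organisms count as common skin commensals, and state whether fungi count. Classify each positive culture from the recorded species and date, blinded to arm. Report any positive culture as a sensitivity result.

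The cost is one definition line and a classification step on species and date, which the article says are documented. Patient care does not change. The small downside is that a few true commensal bacteremias with only one recorded positive culture will not be counted; using dates in place of separate draws adds to these.
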